### Participants

The study population consists of all new families in the four participating municipalities during the study period. The study population of parents is expected to represent the following subgroups: First-time parents (40%), premature births (7%), twin or triplet births (2%), postpartum depressed mothers and fathers (7–14%) and parents with a cultural background other than Danish depending on geographical area (7–20%) [43, 44].

All mothers and biological fathers or maternal partners who are visited by a health visitor 1–2 weeks after birth are eligible for the study. As this is a community-based universal intervention with no expected side effects in which we seek to measure the effect in a natural population of new parents, we have no exclusion criteria except for parents who are undergoing treatment elsewhere or are unable to manage their own legal affairs and are therefore not visited by a health visitor.

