### Randomisation

The cluster randomisation was carried out in June 2016 after receiving the declaration about participation from the municipalities and before the health visitors’ enrolment in the NBO training course. The already established geographical districts within the four participating municipalities where health visitors provide home visits to new families were regarded as clusters (*n* = 17) to avoid a spill-over effect between health visitors and families. Thus, health visitors were allocated to an intervention or comparison group according to their geographical districts, whereas the participating families were allocated according to their health visitor.

Prior investigation of the clusters alias the districts revealed that all districts represented a variation in social status among inhabitants and considerable differences in birth rates; in 2015, from 50 to 200 births. The birth rates were associated with the number of health visitors employed in each district. Because of the relatively small number of clusters, we therefore decided to use a restricted randomisation procedure to achieve balance between the two study arms [57]. The criterion for the restricted randomisation was a geographical balance with all participating municipalities represented by both intervention and comparison districts. Moreover, we attempted to obtain numerical balance with the expected number of births between the intervention and the comparison group. In each municipality, the districts were divided into two groups. For each municipality, the districts were allocated randomly to one of the two treatment groups ensuring that both treatments appeared in each municipality and that the treatment groups had approximately the same expected number of births as the comparison groups. An independent data manager handled the entire randomisation procedure.

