### Statistical methods

Our data analyses will be in accordance with the CONSORT guidelines [58]. Intention to treat analysis will be used to detect the effect of the community-based intervention where participation may vary in the study population of parents. Following the intention to treat principle, mothers and fathers will remain in the group defined by the cluster randomisation. A baseline comparison of pre-defined background variables in the two groups will include unpaired t-tests and Fisher’s exact test. When testing the NBO with treatment as usual, the mean scores and any change in the primary variables across time in the intervention group from pre-test (at 2 weeks) to post-test at3, 9 and 18 months will be compared to mean scores and changes in the comparison group. Supplemental analyses will be performed to identify an intervention effect for subgroups and marginal groups of parents according to parity, preterm delivery and depression symptoms. Analyses will include multiple regression analysis to adjust for pre-randomisation variables such as parents’ age, marital status and educational background. Due to the small number of clusters, the analysis will include adjustment for within-cluster correlation. As we examine a relatively large number of outcomes, we will assess the robustness of our findings by applying methods suitable for multiple hypotheses testing. Finally, we will perform a drop-out analysis and examine the comparability of intervention and comparison group in the trial with respect to differences in received health visitor services.

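### Districts were randomised within four municipalities, but the stated analysis does not name municipality; if outcomes differ between municipalities, standard errors will be too large and tests conservative

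*Protocol article*

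**What the plan says.** The Randomisation section of the protocol article describes 17 districts as the clusters and a restricted allocation: "The criterion for the restricted randomisation was a geographical balance with all participating municipalities represented by both intervention and comparison districts". The allocation itself was done separately by municipality: "For each municipality, the districts were allocated randomly to one of the two treatment groups ensuring that both treatments appeared in each municipality". A second, softer restriction concerned size: "Moreover, we attempted to obtain numerical balance with the expected number of births between the intervention and the comparison group".

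The Statistical methods section plans to compare mean scores and changes from the two-week baseline between arms. It says that regression will "adjust for pre-randomisation variables such as parents’ age, marital status and educational background", and that, because there are few clusters, "the analysis will include adjustment for within-cluster correlation". Neither municipality nor expected births is mentioned. No model is written out, and the method for the cluster adjustment is not named.

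**The concern.** When clusters are randomised within strata, differences between strata are largely balanced across the arms and add little to the real uncertainty of the treatment contrast. An analysis that ignores the strata still counts those differences in the residual between-cluster variance. The estimate varies no more than before, but its reported standard error is too large, confidence intervals are too wide, and the test rejects less often than its nominal 5%.

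With 17 clusters, between-cluster precision limits the trial, so this could matter. Differences between municipalities are plausible. The Participants section expects the share of "parents with a cultural background other than Danish depending on geographical area" to run from 7% to 20%, and the section on health visitors and implementation refers to health visitor leaders from each municipality. The article carries the clustering from the design into the analysis, but not the restriction.

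**Working it through.** **The plan's own figure.** Inputs from the Sample size section: 25% against 17% (a fall of 8 points), 5% significance (taken as two-sided), 80% power, 15% loss, cluster size 200, ICC 0.01.

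- Per arm: [1.960 × √(2 × 0.21 × 0.79) + 0.842 × √(0.25 × 0.75 + 0.17 × 0.83)]² / 0.08² = 406, so 812 in total.
- 812 × 1.15 = 934, as stated.
- 934 × (1 + 199 × 0.01) = 934 × 2.99 = 2793, as stated.

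These figures reproduce and do not depend on municipality. They give the effect size: 0.08 / √(0.21 × 0.79) = 0.196 SD, or 0.08 / √(0.25 × 0.75) = 0.185 SD on the control-arm SD. The simulation uses 0.19.

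**Size of the excess by hand.** Assumptions: 4, 4, 4 and 5 districts per municipality; 2793 / 17 ≈ 164 mothers per district on average, spread evenly from 60 to 268; total variance 1; ICC 0.01. Let *s* be the share of the between-district variance that lies between municipalities. The documents give no value for it.

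- Municipality variance: M = 0.01 × *s*.
- Variance of a district mean within a municipality: W = 0.01 × (1 − *s*) + 0.99 × mean(1/m), where mean(1/m) = ln(268/60) / 208 = 0.0072.
- Without municipality, the residual mean square on 15 degrees of freedom has expectation of about W + M × (17 − 73/17) / 15 = W + 0.85 M. Here 73 = 3 × 4² + 5².
- The treatment contrast itself varies with W only, so the standard error is too large by about √(1 + 0.85 M/W).

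For *s* = 25%: √(1 + 0.85 × 0.0025/0.01462) = 1.07. For 50%: √(1 + 0.85 × 0.005/0.01212) = 1.16. For 75%: √(1 + 0.85 × 0.0075/0.00962) = 1.29.

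**Simulation** under the same assumptions: unweighted regression of district means, 4000 trials per setting, 15 degrees of freedom without municipality and 12 with it.

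| Share *s* | Mean SE, without / with | Excess | Type I error, without / with | Power at 0.19 SD, without / with |
|---|---|---|---|---|
| 0% | 0.062 / 0.062 | 0% | 5.0% / 5.0% | 81% / 79% |
| 25% | 0.062 / 0.058 | 7% | 3.9% / 5.1% | 83% / 85% |
| 50% | 0.061 / 0.052 | 15% | 2.9% / 5.1% | 85% / 90% |
| 75% | 0.060 / 0.047 | 28% | 2.2% / 6.0% | 87% / 95% |

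The 6.0% is simulation error: a rerun with 20,000 trials gave 5.1%. The actual spread of the estimate was nearly the same in both models (0.0542 and 0.0541 at *s* = 50%), so only the reported precision differs. A weighted analysis with 60 to 220 mothers per district gave excesses of 6%, 16% and 27%, and type I errors of 4.3%, 2.7% and 2.1%. With an assumed ICC of 0.05 the excesses are about 0%, 11%, 27% and 59%.

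**Outcomes.** The calculation is for a score compared at one time point. Change from baseline removes stable differences in level between municipalities for KPCS and ASQ:SE. It cannot do so for outcomes that Table 1 lists once: CARE-Index, SDQ and ASQ. For the CARE-Index the sample is small. Reading the text as 90 mothers per arm gives 180 / 17 ≈ 10.6 per district, so W at *s* = 75% is 0.0025 + 0.99 × 17/180 = 0.096, and the excess is √(1 + 0.85 × 0.0075/0.096) = 1.03. At ICC 0.01 that is about 3%.

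**The case against.** The strongest objection is that silence is not exclusion. A reader might infer that the plan leaves municipality out. The documents do not support that: the covariate list is introduced as examples, no model is given, and a condensed article may leave a stratum term to a fuller document that is not shown. This stands, and it limits the point to what follows if the analysis uses only the named terms. Still, every named example is a characteristic of the parents, while municipality is the article's own criterion for restricting the randomisation.

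Second, a reader might take oversized standard errors as certain. They arise only if outcomes differ between municipalities, and no such variance is reported. The Sample size section expects little clustering, the Intervention section says that practice in both groups follows the same national guidelines, and the figures on cultural background concern geographical area and population mix, not outcome. This also stands: the shares above are assumptions, and zero is possible.

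Third, change scores and adjustment for education and marital status would absorb part of any difference between municipalities. That is right for the repeated scales, so the table is nearer an upper end for them. It does not cover comparisons of mean scores or outcomes measured once.

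Fourth, a reader might conclude that the trial is underpowered without the term. At a smaller effect of 0.15 SD, power without municipality is 60% to 64% for shares of 25% to 75%, but that reflects the smaller effect. At 0.19 SD it is 81% to 87%.

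**Conclusion.** The point holds as a conditional loss of reported precision. Allocation was within municipality, and the named analysis terms do not reflect that. If only those terms are used and municipality carries 25% to 75% of the between-district variance, standard errors at ICC 0.01 are about 6% to 27% too large and true type I error is about 4% down to 2%. If municipality carries none, nothing is lost.

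There is no bias and no excess of false positives, so this does not threaten validity. The planned power is not at risk from the omission: without municipality it was above 80% at every assumed share. With municipality it ranged from 79% at a zero share to 95%. These power figures count all 2793 mothers as analysed. The effect is largest for mean-score comparisons in the full cohort and for SDQ and ASQ, and smaller for change scores. The CARE-Index has no baseline to help it, but its small sample keeps the excess to a few per cent unless its ICC is well above 0.01.

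The case for the change is the asymmetry: a small, bounded cost against a possibly larger gain.

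**What to change.** In Statistical methods, state that every comparison between arms includes municipality (four levels) as a fixed effect, with district as the cluster term and small-sample degrees of freedom. In a district-level analysis these are 17 − 5 = 12 instead of 17 − 2 = 15. Use expected births per district as a covariate in a sensitivity analysis only: balance on it was attempted, it did not define strata, and it would take one more degree of freedom. If a fuller protocol or SAP already specifies this, a cross-reference is enough.

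The cost is one sentence and three degrees of freedom, about 1 to 3 points of power if municipalities do not differ. No new data are needed.

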### Statistical methods

Our data analyses will be in accordance with the CONSORT guidelines [58]. Intention to treat analysis will be used to detect the effect of the community-based intervention where participation may vary in the study population of parents. Following the intention to treat principle, mothers and fathers will remain in the group defined by the cluster randomisation. A baseline comparison of pre-defined background variables in the two groups will include unpaired t-tests and Fisher’s exact test. When testing the NBO with treatment as usual, the mean scores and any change in the primary variables across time in the intervention group from pre-test (at 2 weeks) to post-test at3, 9 and 18 months will be compared to mean scores and changes in the comparison group. Supplemental analyses will be performed to identify an intervention effect for subgroups and marginal groups of parents according to parity, preterm delivery and depression symptoms. Analyses will include multiple regression analysis to adjust for pre-randomisation variables such as parents’ age, marital status and educational background. Due to the small number of clusters, the analysis will include adjustment for within-cluster correlation. As we examine a relatively large number of outcomes, we will assess the robustness of our findings by applying methods suitable for multiple hypotheses testing. Finally, we will perform a drop-out analysis and examine the comparability of intervention and comparison group in the trial with respect to differences in received health visitor services.

### Harms

The NBO method developed by Brazelton builds on clinical studies of newborn infants and assumes that they have a range set of skills and social abilities that allow them to communicate with their surroundings [38, 59]. As the method takes as its starting point the newborn infant’s condition and cooperation with the parents, we expect no side effects or risks associated with the intervention for the participating infants or parents.

## Discussion

The protocol describes a cluster-randomised community-based trial on a universal parenting support programme (NBO) currently being rolled out in Denmark. The programme efficiency has not yet been studied in a general population in Denmark or internationally.

The NBO method is a clinically relevant alternative to the non-standardised observation of the newborn infant in health visitor practice. By comparing the effect of the NBO method with usual practice, the study contributes to building a more evidence-based practice for health visitors.

The study is community-based, representing a diverse population of new parents. By including all new parents who receive health visitor services in the participating municipalities, we can measure the effect of the NBO method in a universal context. The study population includes subgroups of new parents. Because of their different characteristics, they may be affected in different ways by having a new-born infant and by the support they receive. This may have implications for the interpretation of any study findings.

The randomisation procedure reflects a trade-off between the theoretically optimal procedure and what was possible in practice in a community trial. The already established geographical districts in the participating municipalities were used as clusters to avoid contamination between newly educated health visitors in the intervention group and health visitors who had not received such training in the comparison group. Restricted randomisation was used to minimise imbalances between treatment arms because the heterogeneous characteristics of the districts regarding birth rates were known prior to randomisation. The reduced degree of randomness introduced by clusters and restrictions may increase the risk of selection bias. However, all districts/clusters were enrolled prior to randomisation, had the same chance of receiving the treatment, and learned at the same time of their allocation. Additionally, achieving balanced study arms in our cluster-randomised trial may contribute to the interpretation of study findings, whereas unbalanced study arms may create methodological problems with inference of certain conclusions [57].

The intention of this community-based trial is to test the NBO method as a preventive intervention for development of early healthy parent-infant interaction in a diverse population of new parents. A monitoring process in clinical practice follows the implementation and dissemination of the method. The outcome is tested on a broad range of health outcomes related to the mother, the father and the infant, as establishing an early relationship between parents and their infant is a common health issue influencing a broad range of subsequent health-related problems.

Results will be prepared for publication in international peer reviewed journals in the fields of public health, developmental psychology and nursing science.

## Abbreviations

ASQ: Ages & Stages Questionnaires
ASQ:SE: Ages & Stages Questionnaires, Social-Emotional
KPCS: Karitane Parenting Confidence Scale
MDI: Major Depression Scale
NBO: New-born Behavioral Observation
SDQ: Strengths and Difficulties Questionnaire
SS: Parental Stress Scale
